### Randomization and Blinding

This trial is a quasi-randomized controlled unblinded trial. After recruitment, participants are assigned to 1 of 3 groups based on sex and age, ensuring that each group has similar sex ratios and age ranges. These balanced groups are then randomly assigned, using the random permutation of integers function from MATLAB (The MathWorks Company Ltd), to 1 of the 3 interventions: Activ4Brain, AE, or control.

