### Blood Sample Collection and Analysis

To examine the effect of the intervention on inflammation and neuroprotection blood markers, blood samples are collected from venous blood (15 mL) in a fasting state in the morning by a registered nurse. A complete blood count is performed using a hematology analyzer (DXH500; Beckman Coulter, USA). Aliquots of plasma and serum samples are stored at −80 °C until further use.

Plasma samples will be quantified by enzyme-linked immunosorbent assay for interleukin (IL)-6, IL-1β, tumor necrosis factor-α, interferon-γ, IL-17, IL-1Ra, IL-10, irisin, and brain-derived neurotrophic factor (Thermo Fisher, UK), while serum samples will be analyzed for insulin growth factor 1, vascular endothelial growth factor, and glial cell line-derived neurotrophic factor (ElabScience, USA) according to the manufacturer’s instructions.

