#### Primary Outcomes

The primary aim of this study is to assess whether the Activ4Brain program leads to improved cognitive function in cognitively healthy older people. We will focus on measures from the cognitive assessment protocol associated with 5 cognitive domains: executive function, working memory, episodic memory, sustained attention, and processing speed. These are our primary outcomes.

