### Data Management and Monitoring Plan

A unique code will be attributed to each participant, and the data will be registered in databases separate from any identifiable information. For each stage of data collection, the validity and integrity of the collected data will be checked by at least 2 researchers. The researchers will validate data ranges and cross-check the entries in the databases.

Due to the trial’s short duration and minimal risks, there will be no requirement for a Data Monitoring Committee or interim analyses.

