## Results

Data collection started in January 2024 and finished in April 2025. Seventy-three individuals (40 women and 33 men) were enrolled in the study and assigned to the 3 groups. The average age was 66 (SD 6) years. Data analyses are ongoing, with the publication of the results estimated for 2026 and 2027.

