The retrospective nature of the publication of this protocol has the objective of providing a detailed description of the methods, ensuring that the information is available for trial replication. However, due to the inherent limitation associated with the fact that the publication of the protocol occurred after the end of data collection and the analysis plans presented were not specified before the data were acquired, the results from the study will be used mainly to generate new hypotheses for future clinical trials. Nevertheless, we expect that integrated cognitive and AE will have a stronger effect on cognition than AE alone [47], and we will treat this analysis as confirmatory. However, it is important to note that we are studying the effects of a novel intervention designed specifically for this study, and we do not have strong convictions regarding which specific cognitive domains will be most affected and which cognitive tests will best capture these effects, particularly when addressing cognitive decline in healthy older people. In fact, a large percentage of studies investigating the impact of this type of intervention on cognition use measures of global cognition such as the Mini-Mental State Examination or the Montreal Cognitive Assessment. These tests, while adequate to help diagnose mild cognitive impairment and dementia, suffer from ceiling effects in the cognitively healthy population [62]. To avoid this problem, this protocol includes measures of cognition more sensitive to subtle changes in cognitively healthy older adults.

Notably, it is possible that this type of intervention might be particularly effective in people with lower physical function and/or lower cognitive function who present a higher potential for improvement. In fact, there is evidence that age-related cognitive decline shows high variability, with some individuals aging better than others [63]. Future studies should explore the impact of the intervention focusing on populations with sedentary lifestyles, lower education levels, or poorer cognitive function.

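### The trial is declared unblinded with no role exempted while the primary scores are unnamed and the plan postdates the data, so remaining cognitive data work could be done with arms visible; masking it would cost little

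*Protocol article*

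**What the plan says.** **Blinding.** The Randomization and Blinding section states: "This trial is a quasi-randomized controlled unblinded trial". No other section masks a test assessor, data checker, laboratory worker or analyst.

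**Primary outcome.** The Primary Outcomes section says "We will focus on measures from the cognitive assessment protocol associated with 5 cognitive domains" and lists the five, but attaches no test score to any of them. The Discussion adds: "we do not have strong convictions regarding which specific cognitive domains will be most affected and which cognitive tests will best capture these effects".

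**Timing and status.** The Discussion acknowledges that "the analysis plans presented were not specified before the data were acquired" and that the results will mainly generate hypotheses. Both it and the Statistical Analysis Plan section nevertheless treat the cognitive comparison as confirmatory, with an expected direction: Activ4Brain better than aerobic exercise alone.

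**Work described as still to come.** The Data Management and Monitoring Plan says "The researchers will validate data ranges and cross-check the entries in the databases". The blood section says "Plasma samples will be quantified by enzyme-linked immunosorbent assay". The Results section, after reporting that collection ended in April 2025, says "Data analyses are ongoing, with the publication of the results estimated for 2026 and 2027".

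**Coding.** Participants receive a unique code, and data are held apart from identifying information. Nothing is said about concealing the arm.

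**The concern.** Lack of blinding during exercise classes cannot be avoided and is not the issue. The issue is what follows collection. The usual protection against arm-aware choices is a plan fixed before the data exist, and the authors say they do not have that. What remains is a set of open choices for the primary outcome (which score represents each domain, how entries are checked, how scripts are written) and a declared expectation of which arm should win. The only statement on blinding rules out nothing.

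The trial is also small: 73 people in three arms, about 24 each. A few decisions on individual scores, or one choice between candidate scores, can matter to a contrast of that size, and a reader of the results could not detect it. Because the comparison is presented as confirmatory, such choices would bear directly on the trial's main claim.

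**Working it through.** **1. The plan's own figure.** The document has no figure on blinding. Its sample size is reproduced only to set the arm size. For the group-by-time interaction, λ = f²·N·m/(1−ρ), with f = 0.25, m = 2, α = 0.05 (Participant Recruitment, Eligibility Criteria, and Sample Size) and ρ = 0.5 assumed because it is not stated. At N = 66, λ = 0.0625 × 66 × 2/0.5 = 16.5 on 2 and 63 df, and power is 0.953, so 66 reproduces. With 10% dropout, 66/0.9 = 73.3, hence 74, and 75 is the next multiple of three. Enrolment was 73, so 73/3 ≈ 24 per arm. None of this supports or refutes the point, and masking changes none of it.

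**2. Illustration: one-arm exclusions.** The documents prescribe no removal of extreme values; this is an assumption made to show sensitivity. Change scores are standard normal, with no true difference, 24 per arm and 200,000 replicates. The lowest values are dropped from the Activ4Brain arm only.

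| Chance of a false result favouring Activ4Brain | 0 dropped | 1 dropped | 2 dropped |
|---|---|---|---|
| Shift in that arm's mean (SD) | 0 | 0.085 | 0.157 |
| One two-arm t test, favourable direction | 2.5% | 5.1% | about 8.7% |
| Significant interaction, Activ4Brain numerically best, time test always passes | 1.7% | 3.7% | 6.6% |
| Same, but no practice gain and Bonferroni time test required | 0.4% | 1.3% | 2.8% |
| Significant interaction and Bonferroni superiority over both controls | 0.1% | 0.3% | 0.8% |

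For scale, the standard error of a two-arm difference is √(2/24) = 0.289 SD. The t-test row is not this trial's rule. The Statistical Analysis Plan section requires a significant interaction, a significant time effect in Activ4Brain, and greater improvement than the controls; the last three rows are readings of that rule.

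**3. Illustration: a general arm-aware shift.** A shift of b SD of change in Activ4Brain alone gives λ = n[(2b/3)² + 2(b/3)²] = 2nb²/3. With n = 24, the interaction test's false-positive rate goes from 0.050 to 0.062, 0.099, 0.167 and 0.400 for b = 0.1, 0.2, 0.3 and 0.5. The documents give no value of b.

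**4. Choice among five scores.** The chance of at least one false significant interaction among five independent scores is 1 − 0.95⁵ = 0.226. Simulation with 22 per arm gives 0.209 at correlation 0.3 and 0.170 at 0.6.

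Under the lenient rule (third row of the probabilities above, independent scores):
- One score fixed in advance: 0.05/3 = 0.017.
- Best of five chosen with arms visible: 1 − (1 − 0.05/3)⁵ = 0.081.
- Best of five chosen by interaction p-value with arms coded: Activ4Brain is the best arm one time in three, so 0.226/3 = 0.075.

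Coding the arms alone barely helps if coded by-group results are seen while scores are being chosen. The list has to be fixed before any by-group result is viewed.

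**The case against.** The strongest reply is that *unblinded* is a truthful label for a behavioural trial, and that who sees what during cleaning and scripting is working detail an article may leave to a fuller document. That stands in part: the article does not say that arm labels will be visible at each later step, and a reader who infers such a rule goes beyond the text. What remains is an unqualified declaration in the section devoted to blinding, alongside unnamed primary scores and a plan that postdates the data.

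Four stronger readings are tempting but unsupported:

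- *That all later work is still open.* Analyses are described as ongoing, and the data checks are tied to stages of collection that have ended. Some or all may be done. The future tense does not settle it.
- *That masking the assays, EEG and pupil work protects the main contrast.* The Assessment Procedures section makes those outcomes exploratory. For the cognitive battery, four of the five instruments are computerised, which probably leaves little scoring judgement; choice of score and entry checks are the exposed steps.
- *That 8.7% is the trial's error rate.* It belongs to a two-arm t test with assumed one-sided exclusions.
- *That masking is free, or the only protection left.* It needs a key holder, relabelling and some delay. Named scores, written cleaning rules and dated scripts are also available.

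It is also fair to say that the open choice of scores is a defect in its own right. If all five domains are tested without correction, the 0.226 stands whether or not anyone is masked.

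**Conclusion.** The point holds in limited form. The protocol declares the trial unblinded without exception in circumstances that make later masking worth more than usual: primary scores unnamed, plan written after acquisition, comparison still called confirmatory, direction expected. Any remaining checks, score choices and scripting for the cognitive outcome could be done with arms visible.

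The actual bias cannot be derived. The illustrations show that the false-success rate could rise several-fold, to a level that depends heavily on how the success rule is read. They assume normal change scores, about 24 per arm, no true effect and one-arm exclusions that the documents do not describe. Nothing in the documents shows that an arm-aware decision has been made. This is a worthwhile, low-cost improvement rather than an error that invalidates the analysis.

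**What to change.** In Randomization and Blinding, state that participants and trainers were unblinded, and add the following for work not yet done:

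1. An existing team member who does not carry out the remaining work replaces the arm variable with neutral codes, applies the plan's 60% attendance filter, and holds the attendance, class and trained-task files apart. These reveal the arm: sessions exist only in the two exercise arms, and the trained-task tests only in Activ4Brain.
2. The list of primary scores and the cleaning rules are fixed and dated before any by-group result is viewed, even under codes.
3. Cleaning and analysis scripts for the cognitive outcome are completed under codes before the key is released.
4. The same applies to remaining EEG and pupil preprocessing and ELISA runs, with a note that this protects exploratory outcomes only.
5. Every outcome already checked or analysed with arms visible is listed as unmasked.

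**Cost.** A recoded arm column and sample labels, a key holder, and a short delay before labelled results are seen. Participant codes already exist, so little new structure is needed. Sample size, α and power are unchanged.

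**Limits.** Steps already done cannot be masked, nor can any knowledge of arm at follow-up testing. A multiplicity rule for the five domains is needed separately.

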### Details of the AEs Programs

The AE and Activ4Brain groups engage in 50-minute exercise sessions of moderate intensity (60%‐80% of maximal heart rate), including a 5-minute warm-up, 40 minutes of AEs, and a 5-minute cool-down. The warm-up period includes similar body movements as the main part of the exercise and dynamic stretching, while the cool-down period consists of static stretching. The main part of the exercise session consists of 4 blocks (Table 1). The sessions of the AE group are composed of a sequence of the four 5-minute blocks of AE repeated twice. In the Activ4Brain group sessions, the blocks consist of 5-minute AEs and 5 minutes of cognitive training (Table 2) and are performed only once per session. The Activ4Brain group performs exercise that includes the same rhythmic movements matched in intensity range and duration to the exercise performed by the AE group. The Activ4Brain participants are instructed to keep moving, marching in place, while performing the cognitive training tasks to maintain the increased heart rate. Each group class is composed of 4 participants with a narrow age range to ensure similar physical and cognitive performance.

**Table 1. T1:** Example of the main body structure of a session for the aerobic exercise group^a^.

Block	Rhythmic body movements	Duration (min)
1	V step Marching in place Step jack	5
2	Arms and knees up Marching in place Box step	5
3	High knee touches (with bounce) Marching in place Bounce sky punch	5
4	Four steps forward and return with back walk Marching in place Sidesteps (2 right-2 left)	5

a The sequence of the 4 blocks, 1 to 4, is repeated twice in the same order to make a total of 40 minutes of exercise.

**Table 2. T2:** Example of the main body structure of a session of the Activ4Brain group, including aerobic exercise and cognitive training.

Block	Activity	Description	Duration (min)
1	Rhythmic body movements	V step Marching in place Step jack	5
1	Cognitive training	Task 1 while marching in place	5
2	Rhythmic body movements	Arms and knees up Marching in place Box step	5
2	Cognitive training	Task 2 while marching in place	5
3	Rhythmic body movements	High knee touches (with bounce) Marching in place Bounce sky punch	5
3	Cognitive training	Task 3 while marching in place	5
4	Rhythmic body movements	Four steps forward, return with back walk Marching in place Sidesteps (2 right-2 left)	5
4	Cognitive training	Task 4 while marching in place	5

In both training groups, music with a tempo of 130 to 135 beats per minute-32 count is used to regulate rhythm and enhance motivation [28]. The heart rate of every participant is monitored during the exercise classes with the Polar Team Pro System (Polar Team Pro; Polar Electro), which enables the simultaneous tracking of multiple participants and the monitoring of the exercise intensity in real time, ensuring adequate exercise intensity across all groups.

### Cognitive Training Tasks

The Activ4Brain program includes cognitive training tasks targeting 5 cognitive domains: processing speed, inhibitory control, selective attention, working memory, and decision-making. To maintain participants’ motivation and ensure that the tasks are challenging as participants improve their skills, the tasks’ difficulty level is increased if the class average accuracy for the previous week exceeds 80%. The cognitive training tasks were designed using Psychophysics Toolbox Version 3 [29,30] in MATLAB. In each session, 4 cognitive domains are trained in blocks of 5 minutes each (Table 2). At the end of each week, participants are sent by email their average performance metrics for that week, consisting of the accuracy in each cognitive training task, median reaction time, and reaction time variability (SD), with a written explanation of the meaning of each measure.

For the cognitive training, each participant is assigned a set of 4 pedals connected to a computer that records the pedal presses and execution time (Figure 2). The pedals are USB foot switches for PC computers (FS2017 Pcsensor USB Foot Pedal Control Switch Keyboard Adapter). Each pedal is assigned a number (1-4) and a color (white, green, blue, or yellow). These are fixed throughout the 24 program sessions (Figure 2). The participants stand side-by-side at the front of the room facing an LCD TV screen where task instructions and visual stimuli are displayed in adequate size. Participants are instructed to respond by pressing the pedals according to each task instruction. Detailed descriptions of the cognitive training tasks are included in Multimedia Appendix 1

**Figure 2. F2:**
[figure not shown]
Schematic view of the cognitive training setup for a class of 4 participants from the Activ4Brain group sessions.

### Assessment of Performance Changes in the Tasks Used in the Cognitive Training Protocol

To assess if the Activ4Brain intervention improved performance on the trained cognitive tasks, the Activ4Brain group is tested before and after the 3-month program on the first difficulty level of the following tasks: processing speed, inhibitory control, selective attention, working memory, and decision-making. The tests are performed in the laboratory, 1 participant at a time, using the same pedal setup but without music or any other instructed movements besides pedal presses. In these tests, we assess task accuracy, reaction time (time from stimulus onset to movement initiation), and execution time (time from stimulus onset to pedal press). To calculate reaction time, we use triaxial ankle accelerometers (BIOPAC Systems). For logistical reasons, these tests are only applied to the Activ4Brain group and will be used to determine if improvements in the trained tasks mediate the cognitive changes observed in the cognitive assessment protocol.

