### Study Design and Intervention Protocol

Our study consists of a 3-arm controlled trial with a parallel study design involving cognitively healthy older people. Participants are allocated into the Activ4Brain group and 2 control groups: an active control group engaged in AE alone and a passive control group, instructed to maintain their daily routines. The passive control group is included to control for the effect of test-retest. The AE group is included to assess if including cognitive training leads to a greater effect on cognition than AE alone and to control for the participants’ motivation to engage in the evaluation sessions, which might be decreased in passive control groups. The group allocation ratio is 1:1:1. The intervention consists of 24 sessions, held twice a week for 3 months. The participants are tested at baseline and after the 3-month training programs (Figure 1).

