### Study Outcomes

#### Assessment Procedures

Study outcomes are assessed at baseline and after the end of the intervention period (3-mo follow-up). Each assessment time point comprises 4 facility-based visits: (1) cognitive assessment (2 h), (2) EEG, pupil, and ECG recording session (2 h), (3) physical evaluation session (30 min), and (4) blood collection. Participants from the Activ4Brain group attend an additional visit to be assessed on the cognitive training tasks used in the program (30 min). The testing sessions end prematurely if the participants show signs of fatigue. Participants are informed of the preparation requirements, which will be checked prior to the assessments.

The study is designed to be powered for the primary outcome only (cognitive function). All secondary and other outcomes—brain and autonomic function (EEG, pupil, ECG), inflammatory and neuroprotective markers, physical fitness and body composition, feasibility and usability, and analyses of the associations between changes in these markers and changes in cognitive function—are exploratory. They are not individually powered and are intended to generate new hypotheses and inform the design of future, adequately powered studies.

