### Statistical Analysis Plan

The study of the effect of the Activ4Brain program on the primary outcome (cognitive function) is confirmatory because we hypothesize, according to previous evidence, that the integrated cognitive-aerobic training program results in larger improvements than AE alone or no intervention (passive control) [47]. All other analyses are exploratory.

Continuous cognitive outcomes will be summarized descriptively with mean (SD) for each group and time. These variables will be analyzed with repeated-measures ANOVA with 1 between-subjects factor (group) and 1 within-subjects factor (time=preintervention vs postintervention). The Activ4Brain intervention will be considered effective in improving cognitive function if the group × time interaction is significant at a level of .05, if the post hoc tests (with CI adjustment using Bonferroni) show a significant effect of time for the Activ4Brain group, and the improvement is higher for this group than for the other control groups. If the data do not meet assumptions of sphericity, the Greenhouse-Geisser correction will be used. Description of the effect sizes by partial η^2^ will follow the following cutoff points: less than 0.06 will be considered a small effect; between 0.06 and 0.14 will be considered a medium effect; and higher than 0.14 will be considered a large effect [48].

Missing data will be assessed prior to analysis. Analyses will be conducted using the available data (complete case analysis), and participants with missing data for a specific outcome variable will be excluded only from the relevant analysis.

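### Trained-task tests given only to the Activ4Brain arm cannot show that the program improved those tasks, or that such improvement mediates its effect on cognition

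*Protocol article*

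**What the plan says.** The section on performance changes in the training tasks gives these tests two uses. The first is an effect of the intervention: "To assess if the Activ4Brain intervention improved performance on the trained cognitive tasks, the Activ4Brain group is tested before and after the 3-month program". The second is a mechanism. The section cites logistics as the reason for the restriction and states: "these tests are only applied to the Activ4Brain group and will be used to determine if improvements in the trained tasks mediate the cognitive changes", meaning those found in the cognitive assessment. Assessment Procedures confirms that no control arm has these data: "Participants from the Activ4Brain group attend an additional visit to be assessed on the cognitive training tasks used in the program".

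Study Design and Intervention Protocol gives each control arm a purpose. Of the passive arm it says "The passive control group is included to control for the effect of test-retest". Of the other it says "The AE group is included to assess if including cognitive training leads to a greater effect on cognition than AE alone".

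On status, the Statistical Analysis Plan section reserves confirmation for the primary cognitive outcome and adds "All other analyses are exploratory". The Discussion repeats that non-primary results generate hypotheses. It does not list the missing control data on the trained tasks as a limitation.

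**The concern.** Both uses are causal. To say that the intervention improved the trained tasks requires knowing what would have happened to those scores without it. To say that this improvement mediates the program's cognitive effect requires, in addition, the effect of allocation on the mediator. The trial has two arms built to supply such comparisons, and neither took these tests.

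What remains in one arm is a pre-post change and a correlation between two change scores. The first can come from having done the test before. The second can come from people who learn quickly or try hard improving on both sets of tests. If the wording stands, a later paper could report a mechanism on the strength of a change that was never compared with anything. That matters because explaining how the program works is a stated aim and the results will be spread over several publications.

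**Working it through.** **The plan's own figure.** The article gives no figure for the trained-task or mediation analysis. Its only sample size is 66, for the primary interaction (f = 0.25, α = 0.05, power 0.95, 3 groups, 2 measures). With λ = f²·N·m/(1−ρ) and an assumed ρ of 0.5, λ = 0.0625 × 66 × 2 / 0.5 = 16.5 on 2 and 63 df. Power is 0.953, against 0.944 at N = 63. So 66 reproduces, and this point does not touch it.

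**Arm size (assumed).** Arm sizes are not given. Under 1:1:1 allocation, 73/3 is about 24, and the calculated sample gives 66/3 = 22.

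**Step 1: what is identified.** Write the expected pre-post change on a trained task in the Activ4Brain arm as P + R. P is the effect of the program. R is everything else that moves the score between two tests: retesting, familiarity with the pedals from the first test, and regression to the mean. A control arm tested twice would estimate R (or, for the AE arm, R plus the effect of exercise), and the difference would isolate the program's contribution. With one arm, only the sum P + R is observed. In model terms, regressing the mediator on an intercept and an arm indicator when every participant has arm = 1 gives a design of rank 1 with 2 parameters. The allocation-to-mediator effect has no unique estimate, and so neither has the indirect effect against AE or passive control. A larger single arm would not change this.

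**Step 2: what a one-arm pre-post test would report.** Set P = 0 and let R be a standardised gain dz. The two-sided paired t-test at 5% rejects with the probability given by a noncentral t with n − 1 df and noncentrality dz·√n. For n = 24 and dz = 0.5, the noncentrality is 0.5 × √24 = 2.45.

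| Assumed retest gain dz | n = 22 | n = 24 |
|---|---|---|
| 0.2 | 15% | 16% |
| 0.3 | 27% | 29% |
| 0.5 | 61% | 65% |
| 0.8 | 95% | 96% |

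The documents give no size for the retest gain, so these values are a range and not an estimate.

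**Step 3: what a within-arm change-change association would report.** Suppose the trained tasks have no causal path to the cognitive tests and a common cause makes the two changes correlate. In simulation, the ordinary correlation test at 5% was significant in 30% of trials for r = 0.3 and 73% for r = 0.5 at n = 24 (28% and 69% at n = 22). With r = 0 it held its level, at about 5%. The test detects the association correctly. The error would be to call it mediation.

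**Step 4: precision of what survives.** For a partial correlation with three covariates (for example both baseline scores and age), df = n − 5 and critical r = t/√(t² + df). At n = 22: 2.110/√(4.45 + 17) = 0.46. At n = 24: 2.093/√(4.38 + 19) = 0.43. Even the descriptive association will be imprecise.

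**The case against.** The best reply is that the article speaks of mediating the cognitive changes observed, not the difference between arms. Two-occasion within-person mediation, with time as the contrast, is an established method and can be fitted in one arm. That stands. A reader might infer from Step 1 that no indirect effect of any kind can be computed here, and the documents do not support that: the result concerns only the effect of allocation. But in the within-person model the exposure is time, which carries the program, the retest and every other change over three months together. It can be estimated, yet it does not answer whether training on the tasks explains what the program does.

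Second, repeated practice is the intervention itself: 24 sessions with four 5-minute training blocks make 24 × 20 = 480 minutes, against one earlier 30-minute test visit. Much of any gain may well be due to training. That is plausible and it limits the worry about the first use, but the share due to retesting is unknown and cannot be learned from these data.

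Third, the text states aims and not conclusions, labels the analysis exploratory, and discloses the one-arm restriction. All true, and it keeps this a matter of moderate weight. The exploratory label deals with power and confirmation, though; it does not supply a missing comparison. Nor could a fuller analysis plan, because the control data were not collected.

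A reader might also take low power to be the fault. It is a separate matter, and Assessment Procedures already concedes that the non-primary outcomes are not individually powered.

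**Conclusion.** The concern holds for the two causal uses of the trained-task tests. The effect of allocation on the trained tasks, and the indirect effect of the program against AE or passive control, are not identified with data from one arm. One-arm models can be computed but cannot separate the program from retesting, pedal familiarity, regression to the mean or common causes.

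The identification result needs no assumption beyond the stated one-arm testing. The rates in Steps 2 and 3 rest on assumed retest gains, assumed common-cause correlations and arms of 22 to 24, and serve only to show scale.

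It would be wrong to infer that the trial's main question is compromised. The cognitive assessment is done in all three arms, and the primary group-by-time comparison, its sample size and its success rule are unaffected.

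**What to change.** Control-arm tests can no longer be added, since data collection ended in April 2025. Replace the mediation aim with wording such as:

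*Within the Activ4Brain group only, we will describe, as an exploratory analysis, the association between change in trained-task performance and change in the cognitive assessment, with 95% CI (for example adjusted for baseline scores); no mediation or causal claim will be made.*

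Reword the first use as a description of pre-post change in the trained arm, and add to the limitations that these gains are not controlled for test-retest effects. The choice of covariates is for the authors, provided it is fixed before the analysis.

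The cost is a change of wording and the loss of one exploratory mechanistic claim. No new data are needed and no other analysis changes.
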